## Background

Postoperative delirium (POD) is a common complication of cardiac surgery [1, 2]. Several studies have already shown that geriatric patients, patients undergoing cardiac surgery, and intensive care patients are at a high risk of developing POD [3–9]. Recent data suggest an age-dependent incidence of post-cardiac surgery delirium: 21.4% of patients aged ≥ 65 suffered from POD, and POD was observed in 33.5% of patients aged > 80 [1]. Patients with delirium are more likely to have a prolonged hospitalization, a pre-existing dementia, and to die during hospitalization [10]. For example, a meta-analysis including almost 2,939 patients showed that delirium is associated with an increased risk of death after an average follow-up of 22.7 months (hazard ratio [HR] 1.95, 95% CI 1.51–2.52), as well as an increased risk of institutionalization (OR 2.41, 95% CI 1.77–3.29) [11]. In several studies, delirium was associated with an increased risk of postoperative cognitive dysfunction and dementia [10–12]. For example, a recent study showed an association between delirium severity and subsequent 3-year cognitive impairment [13]. In patients who experienced the most severe delirium, the rate of cognitive decline nearly tripled [13].

It has recently been shown that surgery, in particular cardiac surgery, is associated with increased markers for neuronal damage and neurodegeneration, such as total-Tau and neurofilament light chain (NfL) [14–17]. These effects, including hypoxemia and disruption of the blood-brain barrier, seem to be caused by the entire procedure and not solely by inhalational anesthesia, as previously hypothesized [18]. It is likely that patients with an underlying neurodegenerative disorder, although still clinically inapparent, might experience a significant “second hit” that accelerates the neurodegenerative processes causing cognitive decline after these interventions. This hypothesis is supported by pre-surgery cerebrospinal fluid (CSF) measurements of Amyloid-β_42_ (Aβ_42_), a key biomarker for Alzheimer’s disease (AD) [19]. Furthermore, Evered et al. report decreased CSF Aβ_42_ levels in patients suffering from cognitive decline after general surgery [19].

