### Study setting and participants

In total, 500 patients aged over 50 years old undergoing cardiac surgery will be recruited at the Department of Cardiovascular and Thoracic Surgery of the University Medical Center Göttingen, Germany. Inclusion and exclusion criteria are summarized in Table 1. Potentially eligible participants will be identified by preoperative schedules. Informed consent will be collected by study team after providing detailed study information and prior to baseline assessment and biomarker sampling. Initially, preoperative screening will be assessed via medical history, a screening questionnaire, and laboratory measurements for identification of risk factors for delirium, cognitive decline, and dementia (t0). Furthermore, delirium symptoms will be assessed over the first five postoperative days (t1), and biomarkers will be measured on the 7th postoperative day (t2) to address the impact on neurodegenerative and neuroinflammatory markers after cardiac surgery. We will provide two follow-up visits for all patients 12 months (t3) and 24 months (t4) after surgery (Fig. 1, Table 2).

**Table 1 Tab1:** Inclusion and exclusion criteria of the FINDERI study

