### Follow-up visit 12 months (t3) and 24 months (t4) after cardiac surgery

The follow-up visits will be performed 12 and 24 months after cardiac surgery. All participants will be invited to an in-hospital visit to be evaluated for new-onset cardiovascular, neurological, or psychiatric disorders, hospitalizations post-surgery (number and reasons of hospitalizations), COVID-19 infection and vaccination status, geriatric check (mobility, statutory level of independency, cognition, psychological symptoms, and previous hospital stay), and to undergo a short 6-item cognitive screening. The patient's current medications, the self-reported SMI, alcohol use, smoking status, and psychiatric symptoms such as hallucinations, tremor, or rigor will also be noted. Furthermore, frailty will be assessed using the CSHA Frailty Scale [38]. Postoperative cognitive impairment or early dementia status will be measured using the MoCA [40], TMTA, and TMTB [34, 41–43].

Furthermore, other neuropsychiatric symptoms will be measured using the following established and standardized instruments (Table 3): Informant Questionnaire on Cognitive Decline in the Elderly (IQCODE) [49–51], Bayer Activities of Daily Living Scale (B-ADL) [52, 53], Movement Disorder Society-Unified Parkinson's Disease Rating Scale (MDS-UPDRS) [54, 55], REM Sleep Behavior Disorder Screening Questionnaire (RBDSQ) [56], and Neuropsychiatric Inventory (NPI) [57].

**Table 3 Tab3:** Neuropsychiatric assessments for follow up visits 12 and 24 months post-surgery

Questionnaire	Description	References
Informant questionnaire on cognitive decline in the elderly (IQCODE)	This shortened 7-item IQCODE is based on a structured interview in which responses of informants (e.g., spouses or relatives of patients) who know the patients well are collected. The IQCODE asks a series of questions about how the patient’s cognition and functioning have changed. Each question is scored from 1 (much improved) to 5 (much worse). For the shortened 7-item IQCODE, a cut-off point (average score) of 3.29 or higher indicates a cognitive dysfunction	[49–51]

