### Statistical analysis

Prognostic quality measures are calculated in order to determine the prognostic properties of continuous endpoints and delirium risk assessment scores in predicting the development of POD, postoperative cognitive decline, and AD. Specifically, a receiver operating characteristics (ROC) analyses is conducted for each of the outcomes and the associated area under the curve (AUC) is reported with optimal cut-off points (simultaneous maximization of sensitivity and specificity, as well as according to Youden). Furthermore, sensitivity, specificity, positive and negative predictive values ​​for the optimal cut-off point are reported. The observed incidence risk factors for the development of POD, cognitive decline, AD, or Lewy body dementia will be investigated using logistic regression or, in the case of time-to-event data, cox regression. Effect sizes are reported as odds ratio or hazard ratio. As far as possible, all key figures are given with a 95% confidence interval. In addition to the univariate consideration of the individual parameters, a multivariate consideration of predictive factors is also planned. For this purpose, machine learning methods for supervised learning are employed (e.g. multivariate logistic regression) and candidate models are trained on a training data set (70% of the data collected). Different models and their corresponding accuracy are compared using a test data set (30% of the data collected). The division of data into test and training data set is random.

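### Every method named for cognitive decline needs a yes/no or time-to-event outcome, although MoCA and Trail Making scores are quantitative, are taken three times, and one aim concerns rate of change

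*Protocol article*

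**What the plan says.** All references are to the protocol article.

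- **Statistical analysis, risk factors.** One sentence covers delirium, cognitive decline, Alzheimer's disease and Lewy body dementia: their risk factors "will be investigated using logistic regression or, in the case of time-to-event data, cox regression". It is followed by "Effect sizes are reported as odds ratio or hazard ratio". No mean difference or slope is mentioned.
- **Statistical analysis, prediction.** A receiver operating characteristics "analyses is conducted for each of the outcomes and the associated area under the curve (AUC) is reported with optimal cut-off points". This needs a yes/no state for each outcome. The section also mentions continuous endpoints, but as predictors whose prognostic value is to be judged, not as outcomes.
- **Statistical analysis, multivariable part.** Here "machine learning methods for supervised learning are employed (e.g. multivariate logistic regression" is the only example, and it is again a binary-outcome model.
- **Follow-up visits.** "The follow-up visits will be performed 12 and 24 months after cardiac surgery", and "Postoperative cognitive impairment or early dementia status will be measured using the MoCA [40], TMTA, and TMTB". Table 2 shows the same three tests at t0, so each has three planned measurements.
- **Preoperative screening (t0).** MoCA is scored out of 30 points and Trail Making is timed in seconds.
- **Study design.** A secondary aim is to find out whether cardiac surgery speeds up cognitive decline in patients with Aβ pathology. The biomarker section calls the data collection longitudinal, and the Discussion lists the two-year longitudinal design as a strength.

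**The concern.** The article collects quantitative scores at three time points and then names only methods that reduce them to a category or an event. This is a stated choice of model family and effect measure, not just a detail left to a fuller plan: an analysis that followed the section as written would report no mean difference and no slope.

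Two things are at stake, both within the secondary aims.

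1. **Precision.** A patient who loses one MoCA point and one who gains three can count the same, and so can a patient just past the cut and one far past it. That discards information needed to detect modest biomarker and risk-factor associations.
2. **Fit to the question.** Acceleration of decline according to Aβ pathology concerns how far scores move apart over time. A single decliner classification answers that only indirectly; a marker-by-visit term in a repeated-measures model addresses it directly.

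**Working it through.** **Plan's own figure.** There is none for cognitive decline. The only computed figure in the article is the sample size for the delirium AUC, which does not bear on this point. The sizes below therefore rest on assumptions.

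**Inputs**

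- Followed patients: 400 = 500 × (1 − 0.20). The 500 and the 20% dropout come from Study sample, where the dropout belongs to the delirium calculation. Using it for long-term follow-up is an assumption.
- Share *p* of patients called decliners: not given. Assumed 50%, 30% and 20%, with 10% as an extreme.
- Change in score roughly normal, and decline defined by a cut on it: both assumed.

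**Information kept after dichotomising.** The asymptotic relative efficiency of a cut normal outcome, compared with the uncut one, is φ(z_p)² / [p(1 − p)], where φ is the standard normal density and z_p the cut point.

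| p | φ(z_p) | Efficiency | 400 patients act like |
|---|---|---|---|
| 50% | 0.399 | 0.159 / 0.25 = 0.637 | 255 |
| 30% | 0.348 | 0.121 / 0.21 = 0.576 | 230 |
| 20% | 0.280 | 0.078 / 0.16 = 0.490 | 196 |
| 10% | 0.175 | 0.031 / 0.09 = 0.342 | 137 |

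**Simulation check.** 600 data sets of 400 patients had MoCA-like scores at baseline and 24 months (between-patient SD 2.5, residual SD 1.5, SD of annual slope 0.7, mean slope −0.3 points per year). A marker changed the slope by 0.15 points per year per SD.

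| Decline defined as a loss of | Decliners | Power, logistic | Power, unadjusted slope | Power, baseline-adjusted score |
|---|---|---|---|---|
| 2 points or more | 29% | 0.44 | 0.65 | 0.69 |
| 3 points or more | 17% | 0.33 | 0.62 | 0.67 |

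Most of the gain comes from keeping the scale; baseline adjustment adds a little. With a marker effect of 0.20, logistic against baseline-adjusted power was 0.68 against 0.91, and 0.57 against 0.93. The simulated scores were neither rounded nor capped at 30. The simulation used the 24-month score only, not a mixed model.

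**If Cox regression were used on visit-detected decline.** Event times would take two values, 12 and 24 months. With true times rounded up to those visits, and an assumed two-year risk of 10% to 30% in the unexposed, the estimated hazard ratios were:

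| True HR | Efron ties | Breslow ties |
|---|---|---|
| 1.5 | 1.47–1.55 | 1.41–1.50 |
| 2.0 | 1.95–2.04 | 1.85–1.98 |
| 3.0 | 2.96–3.09 | 2.55–2.93 |

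Deaths were then added at an assumed 4% per year, 1.5 times that in the exposed and three times after decline. Between 7% and 9% of true declines went unseen, and the Efron estimates were 1.44–1.51, 1.90–2.02 and 2.96–3.02.

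**The case against.** **A binary outcome suits much of the purpose.** The aims speak of predicting the incidence of delirium, cognitive decline or dementia, and AUC, sensitivity, specificity and predictive values require a yes/no state. Efficiency for a mean shift is not the yardstick for classification. This stands, and it is why the ROC and logistic analyses should stay. It does not cover the risk-factor aim or the Aβ aim, which concern association and rate.

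**The size rests on assumptions.** The article does not say that decline will be a cut of MoCA or Trail Making change; IQCODE and B-ADL are also collected. MoCA is bounded, so normality is approximate. This stands, and the figures are illustrations over a range.

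**A fuller plan may name other methods.** Possibly. The point concerns what the article states.

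**Stronger readings that the article does not support**

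- *A reader might infer that Cox regression is fixed for decline seen at two annual visits.* "We will provide two follow-up visits for all patients 12 months (t3) and 24 months (t4) after surgery" makes that natural, but Cox is conditional on time-to-event data, and the sentence is shared by four outcomes, including delirium, which is assessed twice daily. Even if Cox were used for decline, the bias was small with Efron ties.
- *A reader might infer that deaths are mishandled and associations biased by selective survival.* The Background does report that "delirium is associated with an increased risk of death after an average follow-up of 22.7 months" (hazard ratio 1.95). But the article does not say how deaths are treated, an article may leave that to the full plan, and the simulated effect on the hazard ratio was small.
- *A reader might infer a still larger loss for Alzheimer's disease and Lewy body dementia.* These are diagnoses, not described as cuts of a score, so the efficiency formula does not apply to them.

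**Conclusion.** The point holds in a limited form. Every method named for cognitive decline needs a binary or time-to-event outcome, while quantitative scores are available at three time points and one stated aim is about acceleration. If decline is a cut of a roughly normal change score, the loss of information is about 36%, 42% or 51% at 50%, 30% or 20% decliners. With 400 patients followed, that is like analysing 255, 230 or 196. The decliner shares, the number followed and the normal shape are assumptions.

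This is a missed gain in precision and in fit to the question, not an invalid analysis. It affects secondary aims only. Nothing is concluded here about deaths, selective survival or dementia diagnoses.

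**What to change.** For the risk-factor and biomarker aims on cognition, add to Statistical analysis:

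- a linear mixed model of MoCA and of log Trail Making time at t3 and t4, using all available visits;
- adjustment for the t0 score, age, education and, for MoCA, visit mode (in person or telephone);
- predictor-by-visit terms, with an Aβ-marker-by-visit term for the acceleration aim;
- effects reported as mean differences with 95% confidence intervals beside the odds ratios.

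Keep the ROC and logistic analyses for the prediction aim. If Cox regression is used for decline or dementia detected at visits, specify a discrete-time model or Efron ties.

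**Cost.** A wording change, one more analysis and a second effect scale; no new data. Trail Making is not on the telephone list in the follow-up section, so telephone visits add nothing to that model. The mixed model treats unobserved scores as missing at random, which should be stated. All participants undergo surgery, so the Aβ term compares decline between marker levels among operated patients and cannot isolate the contribution of surgery itself.

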### Study sample

In order to plan a subsequent confirmatory study, it is necessary to estimate the necessary parameters with sufficient accuracy. The sample size planning is specifically based on estimating the area under the curve (AUC) of the delirium risk assessment for the occurrence of delirium with a 95% confidence interval so that the 95% confidence interval has a width of approximately 0.05 points. It is assumed that the prevalence of POD is 50% and that there is a true AUC of 0.7. If 416 patients are analyzed, the 95% confidence interval extends approximately 0.025 points from the estimate. To compensate for possible dropouts (assumed dropout rate approx. 20%), 500 patients will be recruited. The calculation was done in nQuery 8.

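### The secondary multivariable models are judged on one random 30% test set, which gives an interval about 1.8 times as wide as the full sample would and a conditional risk of optimism

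*Protocol article*

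**What the plan says.** The Statistical analysis section of the protocol article first sets out ROC analyses of the risk assessment and of continuous predictors, with AUC, cut-offs, sensitivity, specificity and predictive values. It then adds a multivariable analysis using supervised learning, with logistic regression as the example. For that part, "candidate models are trained on a training data set (70% of the data collected"), and "Different models and their corresponding accuracy are compared using a test data set (30% of the data collected"). On how the two sets are formed it says: "The division of data into test and training data set is random". It mentions no repetition of the split, no resampling, no third data set and no correction for optimism.

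The only precision calculation is in the Study sample section and concerns the AUC of the existing risk assessment in all analysed patients. Its assumptions are: "It is assumed that the prevalence of POD is 50% and that there is a true AUC of 0.7". Its result is: "If 416 patients are analyzed, the 95% confidence interval extends approximately 0.025 points from the estimate". It does not cover a model evaluated on 30% of the patients.

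**The concern.** A single random split costs precision twice. The models are fitted on fewer events than the study collects, and their performance is measured on fewer still. The result also depends on one draw of the random numbers. Where the set used to compare competing models also supplies the performance figure, a model taken forward because it came out best carries a figure that is too favourable.

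At stake is the credibility of any multivariable delirium model from this study, and its usefulness as input to the later confirmatory study that the Study sample section has in mind. The primary validation of the existing questionnaire is not at stake.

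**Working it through.** **Inputs from the protocol article.** Analysed 416, recruited 500, AUC 0.70 and prevalence 50% (Study sample); split 70/30 (Statistical analysis). As a lower prevalence I use the Background figure: "21.4% of patients aged ≥ 65 suffered from POD". The trial enrols from age 50, so 21.4% is a sensitivity value and not a forecast.

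**Formula.** Hanley-McNeil, with n1 cases and n0 non-cases:

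SE² = [A(1−A) + (n1−1)(Q1−A²) + (n0−1)(Q2−A²)] / (n1·n0), where Q1 = A/(2−A) and Q2 = 2A²/(1+A).

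At A = 0.70: A(1−A) = 0.21, Q1−A² = 0.5385−0.49 = 0.0485, Q2−A² = 0.5765−0.49 = 0.0865. The 95% half-width is 1.96 × SE.

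**The plan's own figure first.** With 208 cases and 208 non-cases, SE² = (0.21 + 10.03 + 17.90)/43,264 = 0.000650, so SE = 0.0255 and the half-width is 0.050. The stated 0.025 does not reproduce; it would need about 1,660 patients. That discrepancy is a separate matter. Here it means only that the full-sample benchmark is 0.050.

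**Test set of 125 (30% of 416).**
- 50% prevalence, 62 cases and 63 non-cases: SE² = (0.21 + 2.96 + 5.36)/3,906 = 0.00218; SE = 0.0467; half-width 0.092.
- 21.4% prevalence, 27 cases and 98 non-cases: SE² = (0.21 + 1.26 + 8.39)/2,646 = 0.00373; SE = 0.0610; half-width 0.120.

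**Comparison.** The text speaks of the data collected, so the table also shows a split of all 500.

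| Basis | Prevalence | Cases in test set | Half-width, test set | Half-width, same total unsplit | Ratio |
|---|---|---|---|---|---|
| 125 of 416 | 50% | 62 | 0.092 | 0.050 | 1.83 |
| 125 of 416 | 21.4% | 27 | 0.120 | 0.066 | 1.82 |
| 150 of 500 | 50% | 75 | 0.083 | 0.046 | 1.83 |
| 150 of 500 | 21.4% | 32 | 0.110 | 0.060 | 1.83 |

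The ratio is essentially √(1/0.30) = 1.83. A simulation with normally distributed scores gave SE 0.0455 for 62 and 63 patients and 0.0252 for 208 and 208, close to the formula.

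**Events for fitting.** 291 training patients hold about 146 events at 50% (208 in all 416) and about 62 at 21.4% (89 in all 416).

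**Optimism if the best model is kept.** The article gives neither the number of models nor how closely their scores agree, so both are assumed. In the simulation, K models each have a true AUC of 0.70, and the quantity is the mean of the largest test-set AUC minus 0.70. The ranges run from score correlation 0.9 (low end) to 0.5 (high end), with 125 tested.

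| K | 50% prevalence | 21.4% prevalence |
|---|---|---|
| 3 | 0.014 to 0.029 | 0.016 to 0.035 |
| 5 | 0.019 to 0.039 | 0.022 to 0.047 |
| 10 | 0.025 to 0.051 | 0.029 to 0.063 |

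With 150 tested, the values run from 0.012 to 0.057.

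**The word accuracy.** If it meant the proportion correctly classified, then at 21.4% prevalence predicting delirium in nobody scores 1 − 0.214 = 78.6%. A rule with sensitivity and specificity of 0.70 scores 70%. A rule with sensitivity 0.5 and specificity 0.9 scores 0.214 × 0.5 + 0.786 × 0.9 = 81.4%. At 50% prevalence the empty rule scores only 50%.

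**The case against.** The strongest reply is that this is an additional, secondary analysis. The stated primary aim is to validate an existing instrument, and the listed secondary aims are to find risk factors and biomarkers, not to build a prediction model. That stands. A reader might infer that the split undermines the study's main result. The documents do not support this, because the primary ROC analysis is not described as split and the sample size calculation uses all analysed patients.

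A second reply is that the text has models compared, not selected. That also stands. A reader might infer that the reported performance will be biased upward, but that follows only if a winner is carried forward with its test-set figure. If all prespecified models are reported, each test-set estimate is unbiased. The size of any bias rests on assumptions, and equally good models are an unfavourable case.

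Third, accuracy may simply mean predictive performance. The same section lists AUC, sensitivity, specificity and predictive values, and nowhere defines the proportion correct as the measure. The inference that an empty rule would win is too strong: as shown, it beats some informative rules and loses to others, and the problem disappears at the planned 50%.

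Fourth, the 30% is withheld from fitting, not thrown away. Nor do the half-widths show that models cannot be ranked: they describe one model's AUC, whereas two models tested on the same patients form a paired comparison with its own standard error.

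Fifth, an analysis plan that is not shown may add resampling or refitting on all data. That is possible, but the article states the split and the comparison on the test set as the method, and the loss of precision follows from that.

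**Conclusion.** The point holds as one about efficiency and precision in the secondary multivariable modelling. A performance estimate from the 30% test set has a 95% half-width of about 0.09 at 50% prevalence and 0.12 at 21.4% with 416 analysed, or 0.083 and 0.110 if all 500 are split. That is about 1.8 times what the full sample offers. This part rests only on the article's own figures and the Hanley-McNeil formula at AUC 0.70. The loss of 30% of the events for fitting is equally certain.

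The optimism is conditional on selecting a winner and is smaller than the imprecision, at roughly 0.01 to 0.06 AUC for 3 to 10 equally good models with score correlation 0.5 to 0.9. The meaning of accuracy needs clarifying but is not shown to be wrong. I rate the whole as a cheap improvement.

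**What to change.** Replace the single split. Develop the candidate models on all analysed patients and validate internally by bootstrap optimism correction or repeated nested cross-validation. Repeat variable selection, tuning and the choice between candidate models inside each resample. The last of these matters, because picking the model with the best cross-validated or optimism-corrected AUC and then quoting that AUC brings the selection optimism back.

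Compare models on AUC together with calibration or the Brier score. State that accuracy does not mean the proportion correctly classified, which is uninformative if delirium is well below 50%. Leave independent validation to the planned confirmatory study, since a random split within one centre is not external validation in any case.

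The cost is a change of wording in the analysis section, more computing time and more careful coding, with no change to recruitment or data collection. There are two downsides. There will be no held-out set to point to, and the resampled estimate has only approximately the full-sample standard error, so 0.050 and 0.066 are approximate targets and not guarantees.
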